### Design

The SUCCESS trial is a 12-month multicenter pragmatic RCT with a 1:1 allocation to two groups: SUCCESS app plus usual care versus usual care alone.

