### Study Setting

This study will be conducted across six local health districts charged with delivery of health care within the public sector in the Greater Sydney region—Sydney, Northern Sydney, Western Sydney, South Western Sydney, Nepean Blue Mountains, and Illawarra Shoalhaven—including six university teaching hospitals and six community dialysis centers. The Greater Sydney region includes 4,823,991 people (64.5% of the New South Wales population; 20% of the Australian population), of which 38% speak a language other than English at home [19]. The research sites were purposively selected to include broad geographical coverage across Sydney as well as socioeconomic and cultural diversity.

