#### Dialysis at In-Center Units

It is standard practice for patients on hemodialysis at the in-center units to receive dialysis treatment three times a week. Patients receiving in-center dialysis always attend on the same days: either Mondays, Wednesdays, and Fridays or Tuesdays, Thursdays, and Saturdays. Therefore, a pragmatic approach will be used at each center by randomizing patients according to their pattern of attendance. Depending on the center, all participants attending Monday, Wednesday, and Friday will be assigned to the same study intervention group, and those attending Tuesday, Thursday, and Saturday will be assigned to the alternate study intervention group.

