### Sample Size

Our sample size has been calculated based on the primary outcome of the three Health Literacy Questionnaire (HLQ) domains. We assumed a minimal clinically important difference of 0.25 units in any one of the three HLQ domains. A sample size of 384 participants would result in greater than 90% power to detect a 0.25-unit change in an HLQ domain between the two arms, assuming an SD of 0.60, and at least 80% power, assuming an SD of 0.75. These SD values are based on published literature and equate to a standardized difference of 0.42 and 0.33, respectively; a standardized difference of 0.5 is considered a medium effect [33,34]. Our power calculation is based on conducting our analyses using 2-sided tests, a 5% significance level, and assuming 20% loss to follow-up (eg, due to death or kidney transplant).

For qualitative interviews, a maximum total sample size of 40 participants is planned. Interviews will continue until data saturation or until the maximum total sample size is reached.

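### The sample-size section states power on the basis of independent patients, with no stated allowance for in-center allocation by day group; the 80% figure at SD 0.75 has only about 8% variance slack

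*Protocol article*

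**What the plan says.** The Design section describes a "multicenter pragmatic RCT with a 1:1 allocation to two groups". Under Dialysis at In-Center Units, "a pragmatic approach will be used at each center by randomizing patients according to their pattern of attendance": at a given center one three-day pattern receives one arm and the other pattern receives the alternate arm. The in-center unit of randomization is therefore the day group within the center. Under Dialysis at Home, patients are randomized individually. The Study Setting section lists the sites as "including six university teaching hospitals and six community dialysis centers".

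The Sample Size section bases the calculation on the Health Literacy Questionnaire (HLQ) domains: "We assumed a minimal clinically important difference of 0.25 units in any one of the three HLQ domains". For 384 participants it states "greater than 90% power to detect a 0.25-unit change in an HLQ domain between the two arms, assuming an SD of 0.60". Under the less favorable of its two SD scenarios the claim is "at least 80% power, assuming an SD of 0.75". The section adds that the two SDs "equate to a standardized difference of 0.42 and 0.33, respectively". It names two-sided tests, a 5% level and 20% loss as the basis. It mentions no ICC, cluster size, number of clusters, design effect or split between in-center and home patients.

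**The concern.** Patients allocated together in a day group, who share a room and staff three times a week, may have correlated HLQ scores. If so, the in-center comparison carries less information than the same number of independently randomized patients. A power statement whose listed basis omits this correlation describes a different design from the one in the Randomization section.

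What is at stake is how a null result is read. If readers credit the trial with 80% to 90% power for a 0.25-unit difference and the true figure is lower, absence of a detected effect will be taken as stronger evidence of no effect than it is. The SD 0.75 scenario is the more exposed, because its stated power leaves little room.

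**Working it through.** **Inputs from the protocol.** N = 384, 1:1 allocation, 20% loss, difference 0.25, SD 0.60 or 0.75, two-sided 5% (Design; Sample Size). Six hospitals plus six community centers = 12 centers (Study Setting).

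**Assumptions, because the protocol gives no figure.** All 12 centers run both day patterns, giving 24 day groups; 80% of patients are in-center; the ICC of day group within center varies from 0.01 to 0.05; clusters are equal in size.

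**Step 1: reproduce the stated figures.** Analyzed patients: 384 × 0.8 = 307.2, or 153.6 per arm. Standardized differences: 0.25/0.60 = 0.417 and 0.25/0.75 = 0.333, matching the protocol's 0.42 and 0.33. A two-sample t-test with independent patients gives:
- SD 0.60: 95.4%
- SD 0.75: 82.9%

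Both stated lower bounds are met.

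**Step 2: find the slack.** Largest overall design effect = available n per arm / required n per arm.
- 90% at SD 0.60 requires 122.0 per arm: 153.6/122.0 = 1.26.
- 80% at SD 0.75 requires 142.2 per arm: 153.6/142.2 = 1.08.

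**Step 3: allow for day groups.** In-center analyzed patients: 307.2 × 0.8 = 245.8. Home patients: 61.4. Cluster size m = 245.8/24 = 10.24. In-center design effect = 1 + (m − 1) × ICC. Effective N = 61.4 + 245.8/(in-center design effect).

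| ICC | In-center design effect | Effective N | Overall design effect | Power, SD 0.60 | Power, SD 0.75 |
|---|---|---|---|---|---|
| 0.01 | 1.092 | 286.4 | 1.07 | 94.0% | 80.3% |
| 0.02 | 1.185 | 268.9 | 1.14 | 92.6% | 77.7% |
| 0.05 | 1.462 | 229.5 | 1.34 | 88.2% | 71.0% |

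**Step 4: break-even ICC in this scenario.**
- SD 0.75: effective N must stay at 284.5. The in-center part is 284.5 − 61.4 = 223.1, so the design effect is 245.8/223.1 = 1.102 and the ICC is 0.102/9.24 = 0.011.
- SD 0.60: effective N must stay at 244.0. The in-center part is 182.6, so the design effect is 245.8/182.6 = 1.346 and the ICC is 0.346/9.24 = 0.037.

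The normal approximation gives 0.012 and 0.039.

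**Step 5: vary the assumptions.**
- 12 centers, 50% in-center (m = 6.4), ICC 0.05: 93.1% / 78.6% (SD 0.60 / SD 0.75).
- 12 centers, 60% in-center (m = 7.7), ICC 0.05: 91.8% / 76.5%.
- 9 centers (the number of sites where recruitment had begun, per Results), 80% in-center (m = 13.7), ICC 0.05: 85.5% / 67.6%.
- With 9 or 12 centers and 50% to 100% in-center, the break-even ICC for 80% at SD 0.75 runs from 0.005 to 0.032. For 90% at SD 0.60 it runs from 0.016 to 0.13.

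**The case against.** The strongest reply is that the stated powers are lower bounds, and that they hold under modest clustering. In the base scenario at ICC 0.01 both survive (94.0% and 80.3%). The figures alone therefore cannot prove that no allowance was made; any overall design effect up to 1.08 fits both statements. This stands. What supports the point is that the section lists its basis and clustering is not in it.

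Second, both arms are present at every center, so variance shared by the whole center largely cancels. Only correlation within the day group, beyond that of the center, inflates the variance. This also stands, and a center-level ICC put into the formula would overstate the loss. If centers account for a further 5% of variance and the day-group ICC is 0.01, power is about 95% and 82%. It does not settle the matter: the protocol gives no value for the day-group component, and the center random effect in the Data Analysis section models the center, not the day group that was randomized.

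Third, adjusting for baseline HLQ could recover the loss. With an assumed baseline correlation of 0.5, variance is multiplied by 1 − 0.25 = 0.75. Effective N at ICC 0.05 becomes 229.5/0.75 = 306, and power returns to about 95% and 83%. But the Data Analysis section does not name the baseline score as a covariate, and the power section takes no such credit.

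Finally, a condensed article may leave planning detail to a fuller protocol. That would excuse silence about inputs. Here, though, the article prints numerical powers and names what they rest on.

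**Conclusion.** The point holds in a limited form. The power is stated on a basis of independent patients, which does not match the in-center allocation. The 80% figure at SD 0.75 is fragile: it has about 8% variance slack and, with 12 centers and 80% in-center, is lost above a day-group-within-center ICC of about 0.011. The figure of more than 90% at SD 0.60 is sturdier, tolerating a design effect of 1.26, or an ICC of about 0.037 in the same scenario. These break-even values depend on an in-center share and an ICC that the protocol does not give.

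A reader might infer that the design fails to deliver either stated power. The documents do not support that. Both figures hold at ICC 0.01 in the base scenario, and the SD 0.60 figure holds even at ICC 0.05 if 60% are in-center at 12 centers. A reader might also apply 22 cluster degrees of freedom (24 groups minus 2) to the whole comparison and report a larger loss. That is too severe for a mixed design, because home patients are randomized individually. Few clusters do lower in-center power somewhat further, and the restated calculation should address this.

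**What to change.** Restate the power in the Sample Size section for the two-tier design. Give:
- the number of centers and of day-group clusters;
- the expected in-center share and the analyzed patients per day group;
- a range for the ICC of day group within center, for example 0.01 to 0.05, labeled as such so that it is not confused with a center-level ICC;
- the resulting power at SD 0.60 and at SD 0.75, with how the small number of clusters was handled;
- any gain claimed from baseline HLQ adjustment, as a separate line with the assumed correlation.

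N stays at 384 and trial conduct is unaffected. The cost is a rewritten paragraph and a less favorable power statement, chiefly for the 80% figure at SD 0.75.

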### Safety and Monitoring

The research staff team will meet fortnightly with the trial coordinator, project lead, or both to discuss recruitment and ensure that the rights, safety, and well-being of the participants enrolled in the trial are protected. At these meetings, the trial coordinator will verify that study activities and documentation are compliant with the study protocol. The trial coordinator and the research assistants will report any issues to the site-specific principal investigator as they arise. Furthermore, the trial coordinator and research staff team will meet regularly with the site-specific principal investigators and the University of Sydney investigators to report on the trial progress. If a participant is found to experience distress during data collection, the research assistants will have resources available for participants to be referred to the Beyond Blue Support Line, Lifeline, or back to their treating clinicians should they require it.

### Accounting for Extenuating Circumstances

As per the CONSERVE (CONSORT and SPIRIT Extension for RCTs Revised in Extenuating Circumstances) 2021 statement [35], we have outlined our plan if the SUCCESS trial is interrupted due to COVID-19 restrictions (Textbox 2).

Approach to deal with interruptions due to COVID-19 restrictions.
**Extenuating circumstances**
During the COVID-19 pandemic, there have been several occasions when the Australian government has announced lockdowns to reduce the risk of COVID-19 transmission within the community. During these lockdowns, research activities have been put on hold to reduce the risk of COVID-19 exposure to both participants and health professionals. Unfortunately, it is difficult to predict when these lockdowns may occur.
**Impact**
COVID-19 lockdowns may result in a slower recruitment rate and higher rate of participants lost to follow-up due to the inability of research staff to collect data at dialysis centers. Missing data may also arise directly or indirectly due to COVID-19. Procedures for missing data have already been specified in the protocol.
**Mitigating strategies**
Although face-to-face is the preferred approach for data collection for this trial, ethical approval has also been obtained to conduct the trial electronically or virtually. In this case scenario, the blind version of the Montreal Cognitive Assessment will be used, and the Patient-Generated Subjective Global Assessment will be collected at a later timepoint. Therefore, to reduce the interruptions due to COVID-19 lockdowns, the trial will be conducted electronically or virtually.

### Ethics Approval

Ethical approval for this study was granted by the Nepean Blue Mountain Local Health District Ethical Committee as well as the local research governance offices at each of the participating sites (2020/ETH00910).

## Results

Recruitment has begun at nine sites. We expect to finalize data collection by 2023 and publish the manuscript by 2024.The results from the RCT will be submitted for publication to an international peer-reviewed journal, regardless of the findings. In addition, the findings will be disseminated at conferences, and updates will be shared with partners, including participating local health districts, NSW Health, Kidney Health Australia, and consumers. The SUCCESS app will continue to be available to all participants undertaking the trial, after the trial has ended. In addition, the SUCCESS app will also be publicly available on the Apple App Store and Google Play for anyone to download.

## Discussion

This pragmatic RCT, which will be implemented within a real-world setting, aims to determine the effectiveness of a complex health intervention—the SUCCESS app—to improve patient-reported psychosocial and clinical outcomes. Results from previous research by our group suggest that our recruitment strategy will lead to a diverse population, including people from culturally and linguistically diverse backgrounds [16,36] and those with varying levels of cognition and health literacy [37]. In this way, the trial seeks to address limitations of health literacy research conducted to date.

A key strength of this study is that the SUCCESS app is designed to develop transferable skills in health literacy and shared decision-making in a group of patients who have complex needs. That the app has not yet been translated into other languages limits the selection of participants into the trial and the generalizability of findings, and COVID-19 lockdowns across Sydney continue to impact recruitment, data collection, and study timelines.

The management of CKD requires constant patient involvement based on very complex and often difficult-to-understand health advice. If the SUCCESS app is effective, these skills could be applied across multiple decision contexts, such as CKD stages III and IV and those under renal supportive care, and could extend to the management of comorbidities associated with kidney failure. This is a particular strength, given that the majority of patients with CKD have comorbidities, such as cardiac disease, cerebrovascular disease, diabetes, and lipid disorders.

## Appendix

Multimedia Appendix 1 External peer review report from the New South Wales (NSW) Ministry of Health - Translational Research Grants Scheme (TRGS) - TRGS EOI Review Panel (Australia).

## Abbreviations

CKD: chronic kidney disease
CONSERVE: CONSORT and SPIRIT Extension for RCTs Revised in Extenuating Circumstances
CONSORT: Consolidated Standards of Reporting Trials
HLQ: Health Literacy Questionnaire
PG-SGA: Patient-Generated Subjective Global Assessment
RCT: randomized controlled trial
REDCap: Research Electronic Data Capture
SPIRIT: Standard Protocol Items: Recommendations for Interventional Trials
SUCCESS: Supporting Culturally and Linguistically Diverse CKD Patients to Engage in Shared Decision-Making Successfully
